#### Publications

The primary publication for the trial will follow CONSORT guidelines for randomized controlled trials. Criteria for authorship of all papers, presentations, and reports resulting from the study will conform to ICMJE standards.

### Quality Assurance

Multiple mechanisms are in place to assure the fidelity of the intervention and the quality of data collection. Cluster Coordinators, selected by the EmONC Country Team based on their skills, received training and certification on data collection, with refresher training conducted as needed. Cluster Coordinators directly monitor all aspects of the study intervention. The Country Team members visit the participating communities routinely. The DCC performs inter and intra-form edits to assure data consistency and monitors double-data entry. In addition, the DCC statisticians perform data quality reviews on an ongoing basis.

### Data Monitoring Committee, Interim Analyses and Stopping Rule

The NICHD-designated Data Monitoring Committee (DMC) reviews the data including enrollment, compliance, protocol violations, outcomes, and adverse events, at least every six months. Adverse events (including death, life-threatening events, and hospitalization) are monitored by onsite staff, submitted to the DCC and reported to the DMC.

### Statistical Design and Sample Size

The cluster-randomized trial was designed to test the impact of the intervention on perinatal mortality with the cluster as the unit of randomization and analysis. We will test the primary hypothesis that the EmONC will reduce the risk of perinatal mortality (measured as the total number of stillbirths and 7-day neonatal deaths per 1000 deliveries) with a permutation test conducted at the cluster level. Secondary analyses of this same hypothesis controlling for individual-level covariates will be conducted using extensions of the generalized linear model that account for the correlation within cluster. An assessment of whether the 106 possible clusters available provided adequate power to test this hypothesis was conducted under the assumptions that on average the clusters will contribute 300 to 500 deliveries per year with a base mean rate of perinatal death of 40 to 50 per 1,000 deliveries and an intra-class correlation coefficient between 0.005 and 0.01 (based on preliminary data collected from these clusters). Using a two-sided hypothesis test at the 5% level of significance, these 106 clusters will provide a power of at least 80% across the full range of assumptions and greater than 90% across much of the range to detect a reduction of 30% in the perinatal mortality.

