### Enrollment - Trial sites

The study clusters are located at 7 sites in six countries. (Table 1) All of these sites are research units of the Global Network (GN). From 2005 to 2007, five of the seven sites participated in a cluster-randomized trial of WHO Essential Newborn Care and Neonatal Resuscitation, the GN's FIRST BREATH trial [57].

**Table 1 T1:** EmONC trial study sites

Country	Argentina	Guatemala	India		Pakistan	Kenya	Zambia
Site	Corrientes	Chimaltenango	Belgaum	Nagpur	Thatta	Western Province	Kafue
Clusters (n)	6	10	20	20	24	16	10
Total deliveries (n)^a^	2.541	2,518	19,529	4,344	10,404	8,436	6,374
Home deliveries^a ^(%)	1	72	19	14	59	67	57

^a ^The number of total deliveries and percentage of home deliveries are based on data collection over a 1-year period prior to the implementation of the EmONC trial for all sites except Chimaltenango, Guatemala and Nagpur, India, where delays in the approval process limited prior data collection to six months.

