### Randomization procedures

Preliminary data collected by the GN from these 106 clusters formed the basis for randomization. The DCC stratified clusters based on a cross-classification of birth and perinatal mortality rates and randomized within one to three comparable strata to intervention or control cluster within each Global Network site.

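### Neither stated analysis of perinatal mortality uses each cluster's pre-trial rate; adding it inside a within-stratum permutation test would be a cheap, modest gain in efficiency

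*Protocol article*

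**What the plan says.** *Statistical Design and Sample Size* names two analyses of the primary hypothesis. The first is a test of perinatal mortality "with a permutation test conducted at the cluster level"; the section does not say which statistic is permuted, whether the permutation respects strata, or whether any covariate enters. The second is model-based: "Secondary analyses of this same hypothesis controlling for individual-level covariates will be conducted using extensions of the generalized linear model". No cluster-level covariate is mentioned in either.

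*Randomization procedures* shows that cluster-level baseline data exist and were relied on: "Preliminary data collected by the GN from these 106 clusters formed the basis for randomization". It continues: "The DCC stratified clusters based on a cross-classification of birth and perinatal mortality rates and randomized within one to three comparable strata", within each site.

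The footnote to Table 1 (*Enrollment - Trial sites*) gives the length of the baseline: "data collection over a 1-year period prior to the implementation of the EmONC trial for all sites except Chimaltenango, Guatemala and Nagpur, India", where it was six months. By the cluster counts in Table 1, 76 clusters have 12 months of data and 30 have six.

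**The concern.** In a cluster trial, much of the variance of the treatment comparison comes from true differences between clusters. Individual-level covariates reach that component only indirectly, whereas a cluster's own earlier perinatal mortality bears on it directly. The trial has that figure, used it in grouped form (one to three strata per site) to allocate arms, and then names no analysis that uses it. Differences in baseline mortality between the arms can remain within such coarse strata.

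At stake is precision: power for effects smaller than the planned 30%, a narrower interval, and some protection against chance imbalance. Timing matters too. A baseline covariate added after the results are known would carry little weight, so it has to be fixed in advance.

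**Working it through.** **Inputs from the article:** 106 clusters, 300 to 500 deliveries per cluster per year, a base rate of 40 to 50 per 1,000, an ICC of 0.005 to 0.01, a 30% reduction, and a two-sided 5% test. **Assumed:** 53 clusters per arm and one year of accrual, because neither the allocation ratio nor the trial's length is stated.

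**1. The stated power.** Effective births per arm = 53m / (1 + (m − 1)·ICC). At the least favourable point (40 per 1,000, m = 300, ICC 0.01):
- Design effect = 1 + 299 × 0.01 = 3.99, so effective n = 15,900 / 3.99 = 3,985.
- Rates are 0.040 and 0.028, so SE = √[(0.04 × 0.96 + 0.028 × 0.972) / 3,985] = 0.00406.
- 0.012 / 0.00406 = 2.96, and 2.96 − 1.96 = 1.00, so power is 84%.

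Over the grid of two rates, three cluster sizes (300, 400, 500) and two ICCs, power runs from 84.0% to 99.6%, and 9 of 12 points exceed 90%. The article's statement holds without any baseline adjustment.

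**2. How informative the baseline is.** Reliability of a cluster's baseline rate = ICC / (ICC + (1 − ICC)/m). Deliveries per cluster in the baseline period, from Table 1 (reading 2.541 for Corrientes as 2,541):
- Smallest: Nagpur, 4,344/20 = 217, and Chimaltenango, 2,518/10 = 252, both over six months.
- Largest: Belgaum, 19,529/20 = 976.

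Reliability is therefore 0.52 (Nagpur) to 0.83 (Belgaum) at ICC 0.005, and 0.69 to 0.91 at ICC 0.01. The baseline is usable even at the two six-month sites.

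**3. Gain by formula, against a test that ignores strata.** Let c be the correlation between a cluster's true rates before and during the trial (persistence). The correlation of observed rates is r = c·√(R₀R₁), where R₀ and R₁ are the reliabilities of the baseline and follow-up rates, and the variance is multiplied by 1 − r². At the least favourable point with a 12-month baseline, R₀ = R₁ = 0.752:

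| c (assumed) | r | 1 − r² | Power, 30% reduction |
|---|---|---|---|
| no adjustment | – | 1 | 84% |
| 0.5 | 0.376 | 0.859 | 89% |
| 0.8 | 0.602 | 0.638 | 96% |
| 1.0 | 0.752 | 0.435 | 99% |

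At ICC 0.005, power is already 96% or more, so there is little to gain.

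**4. Gain by simulation, with stratified allocation.** The fair comparator is a test that respects the strata. Settings: Table 1 cluster counts, 40 per 1,000, m = 300, ICC 0.01, persistence 0.7, and 0 to 30% of the between-cluster variance lying between sites. Power for a 20% reduction:

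| Strata layout (assumed) | Ignoring strata | Within strata | Within strata, baseline-adjusted |
|---|---|---|---|
| One per site, or reflecting birth rate only | 53–54% | 53–61% | 63–71% |
| Two per site by mortality | 52–54% | 57–66% | 61–70% |
| Up to three per site, ordered on mortality | 52–55% | 59–70% | 61–71% |

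With persistence varied from 0.3 to 0.9, the gain over the within-stratum test is roughly 0 to 18 points for a 20% reduction and −1 to 8 points for 30%. With three strata ordered on mortality it is near zero to 6. The upper ends belong to one stratum per site with high persistence. They are not hard ceilings: they rise somewhat if sites explain none of the between-cluster variance. In a separate run at the planned 30% with persistence 0.8 and up to three mortality strata per site, power was 92.1% ignoring strata, 95.5% within strata, and 97.5% with baseline added. Simulated levels sit above the formula's 84% partly because allocation is stratified and partly because a proportional effect also shrinks cluster variation in the intervention arm; the differences are what matter.

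**5. Type I error.** With no effect, the adjusted test rejected in about 4% to 6% of runs. A test ignoring the strata was conservative, at about 1% to 4.5%.

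**The case against.** The strongest reply is that the article is silent on this point, not wrong. It is a condensed account, the analysis plan is not shown, and covariate lists and permutation details usually sit there. An unadjusted cluster-level permutation test is valid and needs no outcome model, so replacing it is a choice between two sound analyses. At the planned effect the design already meets its stated power, and much of the benefit is available simply by permuting within strata. Most of this stands, and it is why the point is an improvement and not a fault.

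What does not fall away is that the article fixes the covariate level of its adjusted analysis as individual, while describing cluster-level outcome data that it used for design. Making the connection is a specific and cheap change.

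Several stronger readings are not supported:
- **That the baseline goes unused.** It is a stratification factor in the randomisation; only the stated analyses leave it out.
- **That it is the strongest available predictor.** The article reports no correlation between baseline and follow-up rates.
- **That the primary test compares raw rates, or excludes a baseline covariate.** The article does not say either.
- **That the trial is underpowered without adjustment.** Step 1 shows otherwise.
- **That between-cluster variance alone limits power.** At ICC 0.005 and 300 births, reliability is 0.60, so 40% of the variance in cluster rates is sampling variation, which more births would reduce.

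**Conclusion.** The point holds as a recommendation on efficiency. Neither analysis named in the article uses the cluster's pre-trial perinatal mortality, although the data exist for all 106 clusters. Neither the validity of the primary test nor the power claim is in question.

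The benefit is modest and uncertain. Over a within-stratum test it is about 0 to 18 power points for a 20% reduction, an effect the article does not plan for, and about 0 to 8 for the planned 30%. It is close to nothing where persistence is low or the strata already order clusters by mortality, and larger against a test that ignores the strata. These figures are for 40 per 1,000, 300 births and an ICC of 0.01, the least favourable corner of the article's range; elsewhere there is less room to gain. They also rest on 53 clusters per arm, one year of accrual, and assumed persistence and strata layouts, none of which the article gives.

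**What to change.** Unless the analysis plan already does so, pre-specify the following before outcomes are seen by arm:

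1. **Primary test.** Regress each cluster's follow-up perinatal mortality on its pre-trial rate and the site-by-stratum terms, leaving arm out. Permute arm within the site-by-stratum randomisation groups, using the residuals.
2. **Supportive test.** Keep the unadjusted permutation test, also carried out within those groups.
3. **Secondary models.** Add the pre-trial cluster rate to the individual-level covariates.
4. **Baseline length.** State that the pre-trial rate rests on six months at Chimaltenango and Nagpur and 12 months elsewhere, and so is noisier at those two sites.

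The cost is a few sentences of text, minor programming and one degree of freedom. No new data are needed. If persistence turns out to be low, the adjusted test may lose up to about one power point against the within-stratum test.

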### Enrollment - Inclusion Criteria

The clusters have at least 300 deliveries per year with a minimum of 50% occurring at home or first level facilities. This is an intent-to-treat design. Thus all pregnancy outcomes of women who deliver in the study clusters and provide consent are collected.

### Enrollment - Exclusion Criteria

The intervention is intended to work by improving knowledge and affecting behavior change throughout pregnancy. Improved outcomes at delivery will depend on accrued benefits. Women who first move into the study area within 4 weeks of their actual delivery date are unlikely to derive adequate benefit from the intervention and will be excluded from the primary outcome.

### Randomization procedures

Preliminary data collected by the GN from these 106 clusters formed the basis for randomization. The DCC stratified clusters based on a cross-classification of birth and perinatal mortality rates and randomized within one to three comparable strata to intervention or control cluster within each Global Network site.

### Enrolment - Enlisting participants in the trial

The MNH Registry is an ongoing population-based pregnancy outcome data collection program in each of the clusters in the GN's 7 trial sites. The MNH Registry tracks all pregnancies, deliveries and delivery outcomes with its own staff which functions independently from the EMONC trial staff in order to reduce bias due to joint outcome data collection. The Registry in each cluster is managed by a Registry Administrator who, with assistants as needed, screens, enrolls, and tracks all pregnant women within the clusters. They obtain consent for data collection during pregnancy and collect delivery outcomes from all known pregnancies and all deaths of pregnant women up to and including 42 days post delivery/pregnancy termination, and 28-day neonatal outcomes. The Registry collects data during three visits to each mother including an enrollment visit as early as possible within pregnancy (targeted for 20 weeks gestation or greater), a second visit within 48 hours of delivery and a visit at day 42 after birth.

### Data Collection and Management

Outcome and process data are collected separately for the trial. Outcome data are collected through the MNH Registry utilizing standardized instruments to measure maternal demographic data, health care utilization, MNH outcomes and serious adverse events. Data collected for the EmONC trial implementation are collected using standardized instruments in the intervention clusters; process data include cluster team activities, community mobilization activities and training logs. Facility and community-based death audit forms support the activities of the facility trainers and community mobilization teams that utilize them for teaching and discussion.

All data are collected prospectively in the local language using hard copy forms, with only the individual study identification number on each form in order to maintain confidentiality. The forms are keyed into computers at in each country using a common data management system. At intervals ranging from daily to once per week, data are transmitted to the DCC for inclusion in the central database. The hard copy forms are retained in-country in a secure location.

## Discussion

Perinatal mortality and morbidity remains one of the largest challenges for improving maternal and child health in low and middle-income countries. Despite a good understanding of health interventions that can reduce this burden, sustained implementation has been a challenge. A comprehensive package of interventions spanning the continuum of care from the home to the hospital, with a robust community mobilization component, has the potential to significantly improve both maternal and fetal/newborn outcomes. The findings from the current RCT therefore may inform health policy for interventions that are scalable and sustainable in a variety of settings in LMIC.
